##### Secondary outcomes

Cross over of therapy is a binary categorical variable. We will compare the difference in cross-over between groups using Pearson’s chi-squared test. The analysis of the incidence of hypoxemia is performed either with logistic or Poisson regression depending on the distribution. All continuous variables like area under the curve SpO_2_, ISAS score, mean TcCO_2_ and peak TcCO_2_ will be presented as group mean and SD. Univariable analysis using the independent-samples *t*-test will be performed. Further analysis will be done using multiple linear regression. Covariates will be specified as age, gender, BMI, ASA-classification, duration of RFCA procedure, hypotension and BIS. The occurrence of adverse events will be presented as count and percentage per group. Analysis will be performed using a logistic regression model. Likert type questions will be reported as percentage of patients that scored each of the options, stratified by group. The median for central tendency and frequencies for variability are calculated for analysing these descriptive statistics. The response on the Likert type questions will be analysed separately for each question using the Mann-Whitney *U* test.

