#### Intervention description {11a}

All randomised patients will receive standard care with regard to medications used for sedation and physiological monitoring or other interventions to support respiratory function that are considered necessary to be initiated during the procedure by the clinicians. Standard care is consistent with the ESA guideline on Procedural Sedation and Analgesia in Adults [14].

Deep sedation is defined as “A drug-induced depression of consciousness during which patients cannot be easily aroused but respond purposefully following repeated or painful stimulation”. Patients may require assistance in maintaining a patent airway, and spontaneous ventilation may be inadequate.

The physician assistant (PA) anaesthesiology or nurse anaesthetist (NA) administers a combination of analgesics and sedatives to target the level of deep sedation. There will be no restrictions of any dose ranges of the different medications used by the PA/NA. The actual doses of medication used will be registered. The PA/NA will record the doses of sedative medications used during procedures.

Oxygen therapy is administrated as indicated by randomisation. The device used for oxygen supplementation will be different.

For HFNC supplemental oxygen will be given with the Optiflow® device (Fisher and Paykel Healthcare, Auckland, New Zealand). The Optiflow® device has a heated breathing tube and chamber, and a nasal cannula will be used. The gas temperature will commence at high settings (37 °C) and titrated downwards if the patient complains of irritation. The gas flow rate will be started at 10 l/min prior to sedation. The gas flow rate of 10 l/min is usually well tolerated by awake patients. The gas flow will be increased after sedation has been administrated to 50 l/min. The gas flow can be titrated according to patients’ requirements. The flow rate is accommodated according to SpO_2_. The FiO_2_ will be set at 40%.

For LFNC, supplemental oxygen will be given with Microstream® Smart CapnoLine® O_2_. Oxygen supplementation is recommended to start at 5 l/min. The flow rate is accommodated according to SpO_2_. The clinician responsible for the sedation will in case of an upper airway obstruction combine the Microstream® Smart CapnoLine® O_2_ with a nasal or oral airway. The use of a nasal or oral Guedel airway is preferred above multiple airway repositioning to protect the clinician against unnecessary exposure to X-rays.

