### Outcomes {12}

#### Primary outcome

Primary outcome is the lowest SpO_2_. During PSA continuous SpO_2_ measurements will be recorded using SenTec Digital Monitoring with Vsign 2 sensor. Percentage haemoglobin saturated with oxygen will be measured continuously during the procedures as part of routine clinical practice through the anaesthetic monitoring. SpO_2_ monitoring will be measured by the sensor that is placed on the earlobe and recorded continuously.

Timeframe: The time from the first administration of sedative medication to stopping of the sedative medication (= the end of the procedure).

Measure method: Continuous SpO_2_ measurements will be recorded using SenTec Digital Monitoring with Vsign 2 sensor. SpO_2_ will be measured by the Vsign sensor that is placed on the earlobe and will be recorded continuously.

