### Data collection and management

#### Plans for assessment and collection of outcomes {18a}

Baseline characteristics of the participants will be collected. Data such as age, gender, height, weight, medical history and ASA-classification, will be obtained from the medical record. Data from during sedation such as heartrate, blood pressure, bispectral index (BIS), duration of PSA and duration of procedure will be obtained from the anaesthesia record (on-line automatic patient data management system, PDMS). The ISAS questionnaires [4] is a validated questionnaire that measures patient experience with monitored anaesthesia care. Patients respond to eleven statements (e.g. I felt pain) by placing a six-choice vertical response column (e.g. “disagree, moderate”).

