### Statistical methods

#### Statistical methods for primary and secondary outcomes {20a}

##### Primary outcome

The primary outcome parameter is the lowest SpO_2_. SpO_2_ is a continuous variable and will be presented as mean and standard deviation (SD). Univariable between-group analysis using the independent-samples *t*-test will be performed. To adjust for potentially confounding variables, we will perform multiple linear regression analysis. Covariates will be age, gender, BMI, ASA-classification, duration of RFCA procedure, hypotension and BIS. We will impute missing data using multiple imputation with fully conditional specification. The number of imputations will be set to the percentage of incomplete records. All analyses will be performed according to the intention-to-treat principle. All participants who are randomised are included in the statistical analysis and analysed according to the group originally assigned to, regardless of the treatment received.

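### The models for lowest SpO2 and for mean and peak TcCO2 omit the patient's own pre-oxygen value, which costs precision (probably more for TcCO2 than for SpO2) but causes no bias

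*Protocol article*

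**What the plan says.** All places are in the protocol article.

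- Under Statistical methods {20a}, Primary outcome: "The primary outcome parameter is the lowest SpO_2". It is compared by t-test and then by multiple linear regression: "Covariates will be age, gender, BMI, ASA-classification, duration of RFCA procedure, hypotension and BIS".
- Under Statistical methods {20a}, Secondary outcomes: "mean TcCO_2_ and peak TcCO_2_ will be presented as group mean and SD", again followed by a t-test and linear regression on the same seven variables: "Covariates will be specified as age, gender, BMI, ASA-classification, duration of RFCA procedure, hypotension and BIS".
- Under Methods for additional analyses {20b}, no further analyses are planned.
- Under Plans for assessment and collection of outcomes {18a}, the baseline items are given as examples and name neither SpO2 nor TcCO2: "Data such as age, gender, height, weight, medical history and ASA-classification, will be obtained from the medical record".
- Under Outcomes {12}, the window for these outcomes is "The time from the first administration of sedative medication to stopping of the sedative medication (= the end of the procedure". For SpO2, "SpO_2_ will be measured by the Vsign sensor that is placed on the earlobe and will be recorded continuously". TcCO2 comes from the same earlobe sensor.
- Under Intervention description {11a}, for the high-flow arm: "The gas flow rate will be started at 10 l/min prior to sedation".
- Under Sequence generation {16a}, randomisation is stratified by gender only.

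**The concern.** SpO2 and CO2 already differ between patients before any device is applied. The exclusion criteria still admit COPD milder than GOLD III, GOLD III without frequent or recent exacerbation, and BMI up to 32. A patient's own starting value is therefore a natural covariate for a later level of the same variable. The seven listed covariates leave it out, and nothing in the randomisation balances it other than chance.

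A substitute cannot be taken from inside the outcome window. The window opens at the first sedative dose, by which time the high-flow device is already running, so the first value in that arm is post-randomisation and on treatment. The article does not say when low-flow oxygen starts relative to sedation. A usable baseline has to be recorded before oxygen begins and cannot be recovered afterwards.

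The stake is the width of the confidence intervals. It matters most for mean and peak TcCO2. The Background gives enhanced CO2 clearance as part of the rationale for high flow, but the sample size rests on SpO2 alone.

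**Working it through.** **Step 1: reproduce the stated sample size.** Inputs from Sample size {14}: means 95.2% and 99.3% (difference 4.1 points), SD printed as 0.1 without a unit, power 80%, α 0.05. From Trial design {8}: 1:1 allocation. Two-sided testing is assumed because it reproduces the figure.

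n per group = 2 × (1.96 + 0.84)² × SD² / difference².

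Reading 0.1 as a fraction, that is 10 percentage points: 2 × 7.85 × 100 / 16.81 = 93.4, rounded up to 94, the stated number. Power at 94 is 80.3%. Reading the SD as 0.1 percentage points gives 1 per group, so the 10-point reading is used below.

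**Step 2: standard error without a baseline.** SE = SD × √(2/94) = 10 × 0.1459 = 1.46 points.

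**Step 3: effect of a baseline covariate.** With baseline-outcome correlation r, the residual SD is SD × √(1 − r²). Residual variance falls by r² and the SE falls by 1 − √(1 − r²). The documents give no r, so the range is an assumption. The last two columns apply to lowest SpO2, with a 4.1-point difference and an unadjusted SD of 10 points.

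| r (assumed) | Variance reduction | SE reduction | n per group for 80% power | Power at 94 per group |
|---|---|---|---|---|
| 0 | 0% | 0% | 94 | 80.3% |
| 0.1 | 1% | 0.5% | 93 | 80.6% |
| 0.2 | 4% | 2.0% | 90 | 81.8% |
| 0.3 | 9% | 4.6% | 85 | 83.8% |
| 0.5 | 25% | 13.4% | 71 | 90.1% |
| 0.7 | 49% | 28.6% | 48 | 97.6% |

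The percentage reductions hold equally for mean and peak TcCO2. No power can be given there, because the article states neither an SD nor a target difference.

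**Step 4: is chance imbalance an extra error?** A baseline difference of one standard error (not one between-patient SD) shifts the unadjusted SpO2 comparison by r × 1.46: 0.44 points at r = 0.3, 0.73 at 0.5 and 1.02 at 0.7. This is already inside the SE. At r = 0.5 the adjusted SE is 1.263, and 0.729² + 1.263² = 0.53 + 1.60 = 2.13 = 1.459². The baseline part is one component of the variance that the t-test uses, not an addition to it.

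**Step 5: the same check for TcCO2.** Assume an SD of 4, 5 or 8 mmHg (none is stated). The SE at 94 per group is SD × 0.1459 = 0.58, 0.73 or 1.17 mmHg. An illustrative 3 mmHg arm difference is then 5.1, 4.1 or 2.6 standard errors, so it is distinguishable from chance imbalance without any baseline.

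**The case against.** The strongest objection is that nothing here is wrong. The planned tests are valid, the covariates are pre-specified, and choosing others than the baseline value is a legitimate choice that may be less efficient. That stands, and it limits the point to precision.

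Two stronger readings are tempting, and the documents support neither.

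- A reader might infer that an arm difference in TcCO2 could not be told apart from one present before the device was applied. Allocation is randomised 1:1, so any earlier difference is chance, and the standard error covers it (Steps 4 and 5).
- A reader might infer that no baseline is collected. The {18a} list is open-ended and the SPIRIT schedule (Fig. 2) is not shown. Only omission from the stated models is established.

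Three further objections limit the size.

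- The table compares baseline adjustment with no adjustment. The plan already adjusts for age, gender, BMI and ASA class, which may absorb part of the gain.
- For lowest SpO2, r may well be low. The outcome is one minimum over a long sedation, and the Background attributes respiratory events to airway collapsibility and disturbed respiratory drive. The 100% ceiling and the exclusion of sleep apnoea, chronic oxygen therapy, the most severe COPD and BMI above 32 narrow the starting range. At r of 0.2 or less, power moves from 80.3% to at most 81.8%.
- The article gives no set-up time for a stable sensor reading, so the burden of collecting one is a judgement.

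What the objections leave intact is that the covariate lists are written out and omit the starting value, and that no reading inside the window can replace it in the high-flow arm.

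**Conclusion.** The point holds as a matter of efficiency. The stated models for lowest SpO2 and for mean and peak TcCO2 leave out the pre-treatment value of the outcome. The comparison remains unbiased and its test valid.

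The loss depends on a correlation that the documents do not give. Against an unadjusted analysis, the variance forgone runs from 1% at r = 0.1 to 49% at r = 0.7. Against the planned regression it is set by the partial correlation given the covariates already listed. The power figures for SpO2 also rest on reading the printed SD as 10 percentage points.

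That r is higher for TcCO2 than for lowest SpO2 is plausible but assumed. On that basis the case is mainly for the two TcCO2 outcomes, and for the primary outcome the gain may be negligible. This is a cheap improvement, not a correction of an error.

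**What to change.** 1. Record SpO2 and TcCO2 with the SenTec V-sign sensor before any study oxygen is started, preferably before the allocation is opened, so that in an open-label trial the reading cannot be influenced by the arm. If the study schedule already contains such a reading, no new collection is needed.
2. Pre-specify baseline TcCO2 as a covariate in the models for mean and peak TcCO2, and baseline SpO2 in the model for lowest SpO2.
3. Handle a missing baseline within the multiple imputation already planned.

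The sensor is already used for these outcomes, and that it can supply the baseline is an inference from its continuous recording. The cost is one covariate per model, a slightly longer set-up and an occasional missing baseline. The reading is observational and changes no treatment.

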### Interim analyses {21b}

After inclusion of 50 participants in each group we will perform a blinded sample size control with the SpO_2_ data of the participants. The sample size is based on a similar study which compared the HFNC vs LFNC [8]. However, this study was based on a different indication and conscious sedation instead of prolonged deep sedation.

### Methods for additional analyses (e.g. subgroup analyses) {20b}

Additional analyses are not planned.

### Methods in analysis to handle protocol non-adherence and any statistical methods to handle missing data {20c}

All analyses will be performed according to the intention-to-treat principle. We will impute missing data using multiple imputation with fully conditional specification. The number of imputations will be set to the percentage of incomplete records.

### Plans to give access to the full protocol, participant level-data and statistical code {31c}

In case of audits of health authorities and funder or other researchers needing to access data for scientific purposes, we will give access to the full protocol, participant level-data and statistical code.

### Oversight and monitoring

#### Composition of the coordinating centre and trial steering committee {5d}

All researchers will be a part of the trial management committee. Study coordination will be performed by the Department of Anaesthesiology MUMC+. Data acquisition will be performed by 2 members of the research team. Statistical analysis will be performed by the independent statistician

#### Composition of the data monitoring committee, its role and reporting structure {21a}

Clinical Trial Centre Maastricht (CTCM) designed a data monitoring plan for this study. This study has been classified into the *Negligible* risk category. The monitoring tasks are General and Source Data Verification/Review (SDV/R) related tasks. The monitoring intensity can be adapted during the trial. CTCM is independent from the funder and sponsor.

### Adverse event reporting and harms {22}

#### Adverse events

All adverse events reported spontaneously by the subject or observed by the investigator or his staff will be recorded. For example, an adverse event can also be related to a diagnostic procedure (e.g. contrast allergy during the pre-procedure computer tomography) or to an already existing condition (e.g. decompensation cardio based on atrial fibrillation).

#### Serious adverse events

A SAE is any untoward medical occurrence or effect that results in death, is life threatening (at the time of the event), tamponade, requires prolongation of existing inpatients’ hospitalisation, results in persistent or significant disability or incapacity or any other important medical event that did not result in any of the outcomes listed above due to medical or surgical intervention but could have been based upon appropriate judgement by the investigator.

An elective hospital admission will not be considered as a SAE because the participant is admitted for the treatment. Most SAEs are related to the RFCA procedure not to PSA. Considering the severity of the SAEs, they should be reported. The sponsor will report the SAEs through the web portal *ToetsingOnline* to the accredited METC that approved the protocol, within 7 days of first knowledge for SAEs that result in death or are life threatening followed by a period of maximum of 8 days to complete the initial preliminary report. All other SAEs will be reported within a period of maximum 15 days after the sponsor has first knowledge of the serious adverse events.

The investigator will report all SAEs to the sponsor without undue delay after obtaining knowledge of the events, except for the following SAEs: short-term hypoxemia (SpO_2_ < 90% < 180 s), hypoxemia (SpO_2_ < 90% > 180 s) responding on protocol deviation, unexpected extended recovery time > 8 h, unexpected admission on ICU or CCU and the procedure is terminated.

These SAEs will be reported within a period of maximum 30 days. The period of maximum 15 days may be exceeded. All AEs will be followed until they have abated or until a stable situation has been reached. Depending on the event, follow-up may require additional tests or medical procedures as indicated and/or referral to the general physician or a medical specialist. SAEs need to be reported till end of study within the Netherlands.

#### Frequency and plans for auditing trial conduct {23}

Plans for auditing trial conduct are not included. The independent data safety and monitoring committee will provide an assessment of the patient safety and recommendation to the principle investigator and the researchers about the continuation of this trial. The assessment of the data safety and monitoring committee will be communicated to Clinical Trial Center Maastricht. The Ethical Committee of the MUMC+ will be informed via an annual progress report.

#### Plans for communicating important protocol amendments to relevant parties (e.g. trial participants, ethical committees) {25}

In case of protocol modifications (e.g., changes to outcomes, analyses), we will communicate it to the Ethical Committee and trial registry. Protocol amendments will be reported and documented in the Trial Master File.

#### Dissemination plans {31a}

The sponsor and the investigator agreed to publish the results. This is independent of the results of the study. Publication will take place in accordance with the CCMO guideline regarding publication.

## Discussion

Procedural sedation and analgesia has become a common practice given the increasing demand to relieve anxiety, discomfort and pain during invasive diagnostic and therapeutic procedures. In 2018, the Department of Anaesthesiology at MUMC+ performed 2040 PSA procedures. The majority (*n* = 888) of PSA procedures were performed during RFCA and cardiac electrophysiology testing. Our experience is that as the procedure and PSA time increases saturation more often shows a gradual decrease and desaturations occur more frequent. The aim is to prevent patients for desaturations and hypoxemia. BMI as selection criteria was therefore decreased to 32 kg m^−2^ instead of 35 kg m^−2^. And the PSA (and procedure) time is limited to a maximum of 4 h.

To our knowledge, this is the first study to investigate the effects of HFNC during prolonged deep sedation in patients undergoing RFCA. HFNC is increasingly used as a technique for oxygen delivery in procedural sedation and analgesia The effect of HFNC vs LFNC during sedation has been investigated in several small studies. No difference in primary outcomes of oxygen desaturation was reported. The explanation could be the small sample-sizes and the level of sedation. The intervention could have a positive effect in this study because deep sedation is performed in supine position for a prolonged time up to 4 h.

The sample size in this prospective study was calculated and adjusted using a similar study which compared HFNC vs LFNC in a different population [26]. In this study, participants underwent dental surgery. However, the duration of sedation and treatment were shorter (< 75 min), which will affect primary outcome [26]. Therefore, we decided to perform a sample size control.

The secondary outcomes include ratings of experiences of participants and staff using 5 point Likert scales. Validated questionnaires were preferred, but unfortunately these are not available.

To ensure that all colleagues work according to the study protocol and follow GCP guidelines, education and training is provided. The AC are trained to obtain informed consent. The AC are instructed and trained in the use of the Optiflow and Vsign. They are also trained to provide PSA according to this study protocol during sedation. The group of PAs and AC exists of 7 colleagues.

### Trial status

Trial recruitment is started on 15 November 2022. Recruitment will take approximate two years. This is the first protocol version registered on 21 November 2020. We plan to start recruitment by 1 September 2021 and to complete recruitment by 31 August 2023.

## Data Availability

Data can be obtained by contacting the coordinating researcher. Data will be available by contacting by email the coordinating researcher using details on trial published articles. Email for requests: [contact].

## Abbreviations

AF: Atrial fibrillation
CTCM: Clinical Trial Center Maastricht
HFNC: High-flow nasal cannula
LFNC: Low-flow nasal cannula
MUMC+: Maastricht University Medical Center+
NA: Nurse anaesthetist
PA: Physician assistant
PDMS: Patient data management system
RFCA: Radiofrequency catheter ablation
